## Abstract

**Background:**

Perinatal stroke occurs in more than 1 in 2,500 live births and resultant congenital hemiparesis necessitates investigation into interventions which may improve long-term function and decreased burden of care beyond current therapies (http://www.cdc.gov/ncbddd/cp/data.html). Constraint-Induced Movement Therapy (CIMT) is recognized as an effective hemiparesis rehabilitation intervention . Transcranial direct current stimulation as an adjunct treatment to CIMT may potentiate neuroplastic responses and improve motor function. The methodology of a clinical trial in children designed as a placebo-controlled, serial –session, non-invasive brain stimulation trial incorporating CIMT is described here. The primary hypotheses are 1) that no serious adverse events will occur in children receiving non-invasive brain stimulation and 2) that children in the stimulation intervention group will show significant improvements in hand motor function compared to children in the placebo stimulation control group.

**Methods/design:**

A randomized, controlled, double-blinded clinical trial. Twenty children and/or young adults (ages 8–21) with congenital hemiparesis, will be enrolled. The intervention group will receive ten 2-hour sessions of transcranial direct current stimulation combined with constraint-induced movement therapy and the control group will receive sham stimulation with CIMT. The primary outcome measure is safety assessment of transcranial direct current stimulation by physician evaluation, vital sign monitoring and symptom reports. Additionally, hand function will be evaluated using the Assisting Hand Assessment, grip strength and assessment of goals using the Canadian Occupational Performance Measure. Neuroimaging will confirm diagnoses, corticospinal tract integrity and cortical activation. Motor cortical excitability will also be examined using transcranial magnetic stimulation techniques.

**Discussion:**

Combining non-invasive brain stimulation and CIMT interventions has the potential to improve motor function in children with congenital hemiparesis beyond each intervention independently. Such a combined intervention has the potential to benefit an individual throughout their lifetime.

**Trial registration:**

Clinicaltrials.gov, NCT02250092Registered 18 September 2014

## Background

 Based on data and statistics reported by the Center for Disease Control, " Population-based studies from around the world report prevalence estimates of CP ranging from 1.5 to more than 4 per 1,000 live births or children of a defined age range. " Additionally, the lifetime costs of care for an individial diagnosed with cerebral palsy is over 1 million dollars. (http://www.cdc.gov/ncbddd/cp/data.html) [1]. Specific to children, hemiparesis or paralysis on one side of the body, is most commonly caused by an ischemic stroke or vascular disorder, and is often associated with CP [1].

### Significance of diagnosis

Many children with hemiparesis receive rehabilitation, but our current interventions have a limited impact on restoring function. The extended cost and utilization of lengthy formal therapies such as bracing, casting, pharmacologic interventions and surgery can be painful, energy consuming and resource depleting. Treatments such as constraint-induced movement therapy (CIMT) have shown significant improvements in motor function, yet the optimal electrical current dosing in this population has yet to be established [2] Impacting the recovery of a child during critical periods of development with achievement of motor milestones progressing into adulthood is imperative to positively influence an individual who faces the challenges of living with CP. Corticospinal system (CS) development continues postnatally over the first few years of life, and congenital impact or damage to the system before, during or one year after birth can cause detriment to function throughout the individual lifetime [2, 3] Although initially this CS system develops bilaterally in typical development, for those with a perinatal stroke, the integrity of the ipsilateral projections is compromised and control of the limbs occurs from the contralateral hemisphere. This loss is driven by *activity-dependent competition,* between the two hemispheres [4]. As an individual moves and explores the environment through bimanual and unimanual activity, the crossed corticospinal tract integrity gains strength. Typical interhemispheric inhibition is progressively established with potent interaction between the two hemispheric motor cortices and accompanying corticospinal activation and distinct unimanual function.

### Critical barriers to progress in pediatric hemiparesis

If a child incurs a congenital unilateral infarct, the ipsilesional hemisphere may lose the developing crossed-corticospinal tract integrity, while control of bilateral movement may be dominated by the contralesional hemisphere. This adaptation, however, can have a negative impact on the quality and timing of hand function [5, 6]. Surviving neurons in the area of the stroke undergo an imposed dormancy, influenced by the GABA-induced inhibitory effects of the non-lesioned hemisphere; an exaggerated interhemispheric inhibition. No longer does the competition between the two sides exist equally, and an imbalance of use and integrity of CS system occurs. Additionally, in children with congenital hemiparesis who incurred a stroke at or around the time of birth, “developmental disuse” may ensue, wherein the child utilizes the unaffected hand primarily as the preferred hand, with the affected hand utilized in more of an assisting capacity [7, 8]. Without intervention compelling the affected limb to engage in activity, the disability can become continuously more profound and future recovery less possible.

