### Randomization

Each child will be randomized to either the real (intervention) or sham (control) tDCS arm of the study. The randomization will be done by means of sealed envelopes constructed by the study biostatistician using a random number generator. The study coordinator will assign envelopes, in numerical order, to the subjects upon their randomization.

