#### Study protocol

Children will be randomized into two groups: real tDCS/CIMT (intervention) or sham tDCS/CIMT (control). The children will receive 10 continuous weekday sessions of tDCS and CIMT. (Fig. 2) To clarify, we will include only children in whom we can elicit a motor evoked potential (MEP) using TMS applied to the ipsilesional hemisphere. Although by doing so we limit greatly the number of children whom we can include, such conservatism is necessary to proceed in a safe and informed manner with sufficient awareness of the functional topography of each subject’s brain.

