Excitability Measurements using TMS*.* TMS (Magstim, Dyfed, UK) will be used to measure corticospinal excitability in the ipsilesional and contralesional hemispheres. TMS will be delivered with a 70-mm figure-of-eight coil, tangential to head with handle aligned 45 degrees lateral. The assessment will incorporate single-pulse motor threshold, 1 mV and cortical silent period testing. TMS measurements of cortical excitability guided by stereotactic neuronavigation (Brainsight, Rogue Research, Montreal, QC, Canada), will be employed to create a map of the motor cortex from anatomical MRI images obtained at the CMRR. The co-registration of the TMS coil position on the head with the MRI obtained image of the brain anatomy will allow precision in children who have neurologic lesions. All TMS testing will occur in the UMN CTSI by the PI. For this, the child will be seated in a child-sized reclining chair. Surface electromyographic (EMG) electrodes will be attached over the first dorsal interosseous muscles bilaterally, which will record the motor evoked potentials (MEP) resulting from the magnetic stimulation to the M1 region of each hemisphere. Next, the resting motor threshold (RMT) for TMS activation of the target muscle will be determined, and the location of the hotspot defined. If a threshold cannot be elicited within at least the contralesional hemisphere (i.e., no hotspot), the subject will be excluded from the study as position of the tDCS electrodes will be influenced. The RMT will be defined as the lowest amount of stimulation inducing an MEP of at least 50uV on at least 3 of 5 stimulations Cortical excitability will also be tested by administration of 10 TMS pulses, at the minimum stimulus intensity to produce MEPs of 1 mV [44].

CSP will be determined by the subject exerting finger extensor contraction at approximately 30 % of maximum, as guided by a force tracing on a computer display, while a single TMS pulse at an intensity of 150 % of RMT is delivered to the ipsilesional M1 cortex [45, 46]. The resultant CSP will be measured from the onset of the first peak of the MEP to resumption of surface EMG activity with a threshold value of 50 % mean prestimulus amplitude [47].

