#### Intervention

##### tDCS/CIMT intervention group

Children randomly assigned to this group will receive 10 sessions of both tDCS and CIMT on concurrent days over a span of two weeks. As supported by results from our previous computerized modeling pilot, the subject will receive tDCS at the motor hotspot at 0.7 mA current intensity for 20 min [19]. In a primary motor cortex (M1)/supraorbital (SO) montage, the anode will be positioned over the ipsilesional supraorbital region and the cathode positioned over contralesional motor hotspot to induce contralesional cortical inhibition. During this 20 min session, the subject will be involved in CIMT for the paretic hand and arm using a sling. The sling will be applied for a 2-hour period, which incorporates the 20 min tDCS session. The CIMT will be given to the subject on an individual basis for two hours each CIMT treatment day by a CIMT-trained therapist/interventionist. The CIMT treatments will be standardized, consisting of shaping activities for function, range of motion and strengthening of the paretic upper extremity. In addition, children will continue to use their paretic limb during functional activities at home and during a caregiver-supervised home program. This combined treatment of tDCS and CIMT will continue until 10 weekday sessions are completed over the two-week period.

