##### tDCS/CIMT control group

Children in this group will receive the same procedures and home program as the intervention tDCS/CIMT group but, the tDCS device will be set to a specific placebo setting which extinguishes the current after a 30 s to 1 min ramp-up phase and gradually reintroduces the ramp-down at the end of the 20 min session. This feature allows for placebo control and blinding.

Statistical Analysis. There are 3 analysis populations planned. Intent-to-treat (ITT) will include any subject randomized according to their treatment assignment. Per-protocol (PP) will include randomized subjects without major protocol violations and who were compliant (at least 80 % of planned sessions with their treatment assignment. A detailed list of the major protocol violations warranting exclusion from the PP analysis will be determined prior to trial commencement. The Safety population will include all subjects who receive treatment, according to treatment received. We do not anticipate these groups to differ. The safety profile will use the safety population and be primarily descriptive in nature reporting the number and percentage of adverse events for the two treatment groups and include an aggregate breakdown by severity, seriousness, and frequency (within a patient). Within-group analysis of continuous outcomes comparing posttest to pretest will be done with paired t-tests. Between-group analysis of continuous outcomes comparing the mean change from pretest to posttest between treatment groups will be adjusted for baseline values in the fashion of ANCOVA for added precision. The primary analysis will be based on the ITT population with complementary analyses using the PP population. The association between changes in brain excitability/reorganization and motor function will also be evaluated and based on linear regression. P-values less than 0.05 will be considered statistically significant.

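### The plan assumes one common effect and does not use, in allocation or analysis, which hemisphere drives the paretic hand, although pretest TMS records it and the active arm inhibits a hemisphere that may control that hand

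*Protocol article*

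**What the plan says.** All references are to the protocol article.

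- **Critical barriers to progress in pediatric hemiparesis:** after a congenital unilateral infarct the crossed tract on the lesioned side may be lost, and "control of bilateral movement may be dominated by the contralesional hemisphere". The next sentence adds: "This adaptation, however, can have a negative impact on the quality and timing of hand function".
- **tDCS/CIMT intervention group:** one montage for the whole active arm, with "the cathode positioned over contralesional motor hotspot to induce contralesional cortical inhibition".
- **Eligibility by MEP:** the Inclusion criteria accept a contralesional MEP with or without an ipsilesional one. The paragraph on excitability measurements agrees: "If a threshold cannot be elicited within at least the contralesional hemisphere (i.e., no hotspot), the subject will be excluded from the study". The Study protocol section says something else: "we will include only children in whom we can elicit a motor evoked potential (MEP) using TMS applied to the ipsilesional hemisphere".
- **Excitability measurements:** "Surface electromyographic (EMG) electrodes will be attached over the first dorsal interosseous muscles bilaterally", and the motor area of each hemisphere is stimulated.
- **Randomization:** "The randomization will be done by means of sealed envelopes constructed by the study biostatistician using a random number generator". No stratification factor is named.
- **Statistical Analysis (within the control-group section):** "Between-group analysis of continuous outcomes comparing the mean change from pretest to posttest between treatment groups will be adjusted for baseline values". A separate regression relates changes in excitability or reorganisation to motor function. It uses neither the baseline driving hemisphere nor a treatment comparison by it.
- **Sample size/power:** one between-group AHA difference of 5.4, SD 7.1, correlation 0.8, 10 per group, two-sided 0.05, 80% power.

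**The concern.** The treatment rationale is to reduce contralesional inhibition so that the lesioned hemisphere can drive the paretic hand better. That presupposes a lesioned hemisphere with some usable drive to the hand. The background allows that in some children the opposite hemisphere has taken over, and the Inclusion criteria would let them in. In such a child the stimulated hemisphere may be the one moving the paretic hand, so there is reason to doubt that the effect matches that in other children.

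If the effects differ, a single real-minus-sham mean is hard to read. A null result could mean no effect anywhere, or benefit in some children diluted by others. A positive mean could coexist with children whose paretic hand got worse. With 20 children, chance imbalance between arms on such a factor is also likely. The distinguishing measurement is already taken before treatment, but no stated allocation or between-group analysis uses it.

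**Working it through.** **1. The plan's own figure.** Inputs from Sample size/power: SD 7.1, correlation 0.8, n = 10 per group, difference 5.4, two-sided 0.05.

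- Residual SD = 7.1 × √(1 − 0.8²) = 7.1 × 0.6 = 4.26.
- Standard error of the difference = 4.26 × √(2/10) = 1.905.
- Normal formula, as the plan uses: 5.4/1.905 − 1.96 = 0.874, so power is 80.9%. The stated 80% is reproduced.
- Noncentral t with 17 residual df (20 children less intercept, arm and baseline): 76.2%. This is the reference below.

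**2. Dilution.** Let q be the share of children whose paretic hand is driven contralesionally and e their effect. Neither is in the documents, so both are assumptions. Pooled effect = (1 − q) × 5.4 + q × e. For e = 0:

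| q | Pooled effect | Power, t (17 df) | Power, normal formula |
|---|---|---|---|
| 0 | 5.40 | 76.2% | 80.9% |
| 20% | 4.32 | 57.1% | 62.1% |
| 30% | 3.78 | 46.5% | 51.0% |
| 50% | 2.70 | 26.7% | 29.4% |

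The SD is held fixed. Allowing for the added between-child variation lowers power further: by the normal formula with e = 0, from 62% to 57% at q = 20% and from 51% to 45% at q = 30%.

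**3. Chance imbalance.** Suppose 6 of the 20 children have the pattern and allocation is 10/10 without stratification. By the hypergeometric distribution, a split of 4:2 or worse has probability 63%, and 5:1 or 6:0 has probability 14.1%.

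**4. What the proposed covariate costs and gains.** One more parameter takes residual df from 17 to 16 and power at 5.4 from 76.2% to 75.8%. In simulated trials with e = 0, where the covariate absorbs some of the heterogeneity, power moves from about 50% to 53% (q = 20%) and from about 39% to 41% (q = 30%). The gain is small, because the model still estimates one average effect.

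**5. What by-class estimates can show.** With a common residual SD of 4.26 and 15 df (t = 2.131), the 95% half-width is 2.131 × 4.26 × √(2/m) for m children per arm in a class: 5.7 points for m = 5 and 7.4 for m = 3. Both exceed 5.4. By the normal formula, an interaction test with 5 children per cell has 29% power for a 5.4-point difference in effect and needs a 10.8-point difference for 81%.

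**The case against.** **The protocol expects inhibition to help.** This is the strongest point. The background calls contralesional dominance detrimental to hand function, describes exaggerated inhibition of the lesioned side, and under Promising potential lists reducing that inhibition as therapeutic. A reader might infer that the trial averages opposite effects, or that its own mechanism predicts a loss in these children. The documents support neither. No sentence says that the effect reverses, and the background only says that contralesional control may occur. The objection stands against that stronger reading. It does not establish that the effect is the same in all children, which is what the power calculation assumes.

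**The Study protocol section requires an ipsilesional MEP.** If that rule governs, children with only a contralesional response are excluded and q may be small. But it conflicts with the Inclusion criteria and the excitability paragraph, so it cannot be taken as settled. Nor does it exclude children with an ipsilesional response whose paretic hand is also driven from the other side. Conversely, a contralesional MEP at screening need not be in the paretic hand, so the looser rule does not by itself prove contralesional control.

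**Significance of diagnosis says limb control after perinatal stroke comes from the contralateral hemisphere, with ipsilateral projections compromised.** Read relative to the limb, this sits awkwardly with the next section; read relative to the lesion, it agrees. The text does not settle it.

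**The size is conjecture.** True of q and e. The 5.4 comes from an earlier rTMS/CIMT study and may already average over mixed children, so assigning it only to the others may dilute twice. With that study's SD of 4.7 and correlation of 0.97, power at a pooled 2.7 would exceed 99% with the SD held fixed, and be about 71% if the added heterogeneity is simulated. The loss of power is therefore an illustration under the plan's conservative inputs.

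**The SAP may cover it.** Descriptive subgroups could well be there. The allocation half of the point is stronger, because the article describes the method without any factor.

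**Twenty children cannot resolve this.** Correct as to testing. It limits the remedy to design balance and descriptive reporting.

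**Conclusion.** The point holds in a limited form. The rationale and the Inclusion criteria allow children whose paretic hand is wholly or partly driven by the hemisphere that the active arm inhibits. The plan assumes one effect for all, and its stated allocation and ANCOVA leave out a relevant baseline factor that it already measures. The effect in these children could be smaller, nil or opposite, so the pooled mean may mix different effects.

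The size is unknown. It depends on q, on the effect in these children, and on which MEP rule applies; under either rule mixed control remains possible. The fall from 76.2% to 57.1% or 46.5% rests on assumed shares of 20% and 30%, zero effect in them, and the plan's SD of 7.1 and correlation of 0.8. This is a worthwhile and cheap improvement. It does not show that the primary comparison is invalid: chance imbalance on the factor is already part of the randomised test's error rate.

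**What to change.** 1. Reconcile the MEP statements in the Inclusion criteria, the Study protocol section and the excitability paragraph, and clarify the two background statements on which hemisphere controls the paretic hand. Which version is right is for the investigators to settle.
2. From pretest TMS, before randomisation, classify each child by paretic-hand response in two levels. If a contralesional MEP suffices for entry: ipsilesional response present versus contralesional only. If an ipsilesional MEP is required: with versus without an additional contralesional response. State in advance where a child with no paretic-hand response from either side is placed.
3. Pre-specify this class as a covariate in the between-group ANCOVA. If the envelope list has not been made, also randomise within the two levels.
4. Pre-specify, labelled descriptive only, the real-minus-sham AHA difference with 95% CI in each level, and a listing by arm and level of every child whose AHA or grip strength falls. No interaction test.

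**Cost:** protocol and SAP wording, with no new procedure. One residual df is spent, and the within-level intervals will be wide, about 6 to 7 points either side. The covariate does not itself separate benefit from harm; only the by-level results and the listing bear on that, and only descriptively. No change of montage or of who is treated is proposed.

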### Promising potential

Encouragingly, the nervous system of a child is plastic [9]."The ability to reestablish a balance between the two hemispheres can therefore be exploited by the following therapeutic interventions of 1) voluntary activation of the involved hemiparetic limbs, 2) electrophysiologic decrease in the exaggerated inhibitory activity of the nonlesioned hemisphere upon the lesioned hemisphere, or 3) direct electrophysiologic activation of the lesioned hemisphere [3] Such potential has been seen, using combined interventions of CIMT and non-invasive brain stimulation (NIBS) and as demonstrated through cortical excitability, imaging and motor mapping studies [10]. This work shows promise for outcomes in the pediatric population with the positive potential to influence function throughout the lifespan. Considerations of safety, cost and efficacy are paramount, with further translational consideration of clinical applicability.

### CIMT

CIMT involves constraining the less-affected or non-paretic upper extremity while activating the clinically more-affected or paretic upper extremity through intensive, structured manual therapy [11]. Day camp models, wherein subjects engage in continuous training while wearing a constraint, have been published previously [12, 13] Such a design allows scheduling of therapy content based on themes and activities within a group setting. Subjects perform activities under the guidance of a therapist or trained/supervised interventionist, with incorporation of established goal setting and attainment.

